# The PROCEM study protocol: Added value of preoperative contrast-enhanced mammography in staging of malignant breast lesions - a prospective randomized multicenter study

**DOI:** 10.1186/s12885-021-08832-2

**Published:** 2021-10-18

**Keywords:** Breast cancer, Preoperative staging, Contrast-enhanced mammography (CEM), Randomized trial, Extent estimation, Mastectomy, Partial mastectomy

## Abstract

**Background:**

Correct preoperative estimation of the malignant extent is crucial for optimal planning of breast cancer surgery. The sensitivity of mammography is lower in dense breasts, and additional imaging techniques are sometimes warranted. Contrast-enhanced mammography (CEM) has shown similar sensitivity and in some cases better specificity, than magnetic resonance imaging (MRI) in small, observational studies. CEM may be more cost-effective than MRI, and may provide better identification of the tumor extent, however, no randomized trials have been performed to date to investigate the added value of CEM.

In a feasibility study, we found that the treatment was changed in 10/47 (21%) cases after additional CEM. The purpose of the present study is to evaluate the added value of CEM in preoperative staging of breast cancer in a randomized study.

**Method:**

This prospective randomized study will include 440 patients with strongly suspected or established diagnosis of breast malignancy, based on assessment with mammography, ultrasound and core biopsy/cytology, and for whom primary surgery is planned. Patients will be randomized 1:1 using a web-based randomization tool to additional investigation with CEM or no further imaging. The CEM findings will be taken into consideration, which may lead to changes in primary treatment, which is the primary endpoint of this study. Secondary endpoints include rate of reoperation and number of avoidable mastectomies, as well as a cost-benefit analysis of additional CEM. Patient-reported health-related quality of life will be investigated at 1 year with the validated Breast-Q™ questionnaire. The rate of local recurrence or new cancer ipsi- or contralaterally within 5 years will be assessed from medical records and pathology reports.

**Discussion:**

The aim of this trial is to explore the added value of CEM in preoperative staging of breast cancer. The results obtained from this study will contribute to our knowledge on CEM as an additional imaging method to standard investigation with digital mammography and ultrasound. The findings may also provide additional information on which patient groups would benefit from CEM, and on the economic aspects of CEM in standard preoperative practice.

**Trial registration:**

This trial is registered at clinicaltrials.gov, registration no: NCT04437602, date of registration: June 18, 2020.

**Supplementary Information:**

The online version contains supplementary material available at 10.1186/s12885-021-08832-2.

## Background

Suspicion of breast cancer is in most cases raised either by screening mammography or by clinical symptoms. Regardless of the method of detection, “triple assessment” should be performed. This includes clinical examination, breast imaging, and finally cytological or histological investigation to determine whether the finding is malignant or benign. In screening mammography, two projections of the breast are used, the cranio-caudal and medio-lateral oblique, while in the diagnostic work-up the medio-lateral view is added, and additional special projections may also be acquired. The sensitivity of diagnostic mammography is about 85% [1]. The sensitivity of diagnostic mammography is known to be lower in breasts of high density [2, 3], in younger patients [2, 4], and for lobular breast cancer [5].

Additional ultrasound (US) in the work-up of suspicious breast malignancy is particularly helpful in characterizing palpable and non-palpable masses, guiding biopsy of non-palpable lesions, and staging nodal status in the axilla [6]. The additional value of US has been found to be especially high in young women, the majority of whom have dense breasts. In an Irish study of 120 women aged under 40 years, the sensitivity was reported to be 95.8% for ultrasound and 87.5% for digital mammography (DM) [4]. It is, however, important to note that the added value of hand-held US depends largely on the experience of the examiner. Accurate preoperative delineation of the tumor is important in optimizing the results of surgery and reducing the risk of reoperation and unnecessary mastectomy. It has been reported that US provides better estimates of the extent of the tumor than DM [7, 8], although both methods were found to underestimate the extent of the tumor compared with the results of histopathological examination [7].

Due to the limitations of DM and US, additional imaging is required in certain cases. Dynamic, contrast-enhanced magnetic resonance imaging (MRI) is so far the method with the best sensitivity in detecting an invasive cancer, and it is not affected by breast density [2]. Preoperative MRI as a complement to DM and US has shown higher sensitivity in revealing the index cancer, improved size estimation, especially in invasive lobular cancer, and improved ability to detect additional ipsilateral or contralateral malignant foci [2, 9]. However, the patient benefit of detecting small additional foci is not clear when using modern adjuvant therapy [2].

The specificity reported for MRI varies from 47 to 97% [10], and there is uncertainty concerning the long-term effects of the contrast agent used, gadolinium [11, 12]. Furthermore, MRI is a resource-demanding method. The availability of equipment may vary, and MRI-guided biopsy is not possible at many units. This may be a problem, as MRI-located masses can be difficult to identify in US-guided biopsy. In the preoperative setting, additional MRI has been found to reduce the reoperation rate and lead to changes in the treatment plan in 18% of cases in a group of women younger than 56 years [13]. However, two other randomized studies failed to show any benefit of MRI regarding reoperation rate [14, 15].

Contrast-enhanced mammography (CEM) is a relatively new technique in breast imaging. A contrast agent is also used in CEM to image the neo-angiogenesis in breast tumors, enhancing the tumour area. An intravenous iodinated contrast agent is administered at the same dosage as in computed tomography. During an interval of 2–7 min after the injection, high- and low-energy images are acquired of each breast in 2–3 standard projections. Final images of the enhancement are obtained using a subtraction technique. CEM is performed using dedicated software with conventional mammography systems, and standard mammography projections. The findings can be identified by second-look ultrasound or stereotactic mammography for biopsy.

CEM has been used for the past 5 years at several breast centers in Europe and in the USA. Only observational studies on relatively small numbers of selected patients have been published, showing a sensitivity of about 95% and a specificity of 75–80% [16, 17]. CEM has also been reported to provide better delineation of the extent of malignant changes than mammography [11, 18], even in the presence of micro calcifications [19]. Previously published studies comparing the estimated preoperative extent of lesions using CEM and histopathological examination have included between 30 and 118 patients [11, 17–20]. A retrospective study in France showed that the use of CEM in post-screening assessment led to changes in the diagnosis and treatment strategy in 41/195 (21%) of cases with suspicious and undetermined findings on DM and/or US, for example, more extensive surgery or neoadjuvant therapy when additional malignant lesions were found at CEM, or avoiding further biopsies in cases with negative CEM findings [16]. A retrospective review of 101 patients who had undergone surgery for breast malignancy revealed that the surgical procedure had been changed in 20 cases (20%) after additional CEM [21]. In that cohort, 14 patients received neoadjuvant therapy and 41 patients had also undergone MRI. There is thus a need for larger prospective randomized studies on CEM to improve the level of evidence regarding the added diagnostic value of CEM and its effects on staging and choice of treatment in breast cancer.

### Results of the feasibility study

In preparation for this prospective randomized trial, a feasibility study was conducted in 47 patients at the Unilabs Breast Centre, Skåne University Hospital in Lund [22]. The primary treatment plan was changed in 10/47 cases (21%): mastectomy instead of partial mastectomy due to multifocal cancer in three patients and due to larger unifocal extent in two patients; partial mastectomy instead of mastectomy due to improved demarcation of the tumor in one patient; bilateral surgery due to findings of contralateral cancer in two patients; and neoadjuvant treatment instead of primary surgery in two patients. Agreement with histopathological findings regarding preoperative estimation of the size of the malignant changes was better with CEM (Bland Altman statistics: mean difference − 1.36, SD ± 18.45) than with mammography (− 4.18, SD ± 26.20) and ultrasound (− 8.36, SD ± 24.30). No difference was found in the added value of CEM with age, breast density, type of cancer or the presence of micro calcifications.

## Methods

### Aims and endpoints

The aim of this study is to evaluate the added value of CEM in standard clinical preoperative staging of breast cancer regarding potential changes in the treatment plan, the number of (unnecessary) mastectomies and the frequency of reoperation. Furthermore, we will assess whether the potential added value of CEM is influenced by age, pre−/postmenopausality, breast density, type of cancer, the presence of micro calcifications and mode of detection (screening or clinical symptoms).

#### Primary endpoint

Do preoperative CEM findings lead to significant changes in the primary treatment plan?
Mastectomy instead of partial mastectomy, or vice versaBilateral surgery instead of unilateral surgery due to findings of contralateral diseaseNeoadjuvant therapy instead of primary surgeryAxillary clearance instead of sentinel node biopsy

#### Secondary endpoints

Do preoperative CEM findings affect the frequency of reoperation or the number of pathologically avoidable mastectomies?Does preoperative CEM show better accuracy in tumor size estimation than mammography and ultrasound, in comparison with histopathological examination?Do other factors such as age, postmenopausality, breast density, type of cancer, or the presence of micro calcifications influence the added value of CEM regarding changes in the treatment plan and tumor size estimation?Is there a difference in health-related quality of life between patients that have undergone preoperative CEM and those who have not?What are the costs and benefits of additional CEM in a health-economic perspective?Does preoperative CEM affect the number of loco regional recurrences/ipsilateral new cancers or contralateral cancer within 5 years?

### Study design

This is a prospective randomized multicenter trial. The primary endpoint could have been addressed in a prospective cohort study, but most secondary endpoints need a control group to be answered, explaining the chosen study design. A prospective randomized trial also reduces the risk of selection bias.

### Patient enrollment

Potential participants in this prospective multicenter trial will be identified at preoperative multidisciplinary team (MDT) conferences after diagnostic work-up of suspicious breast cancer detected by mammographic screening or clinical symptoms. The study will include 440 patients with strongly suspected or an established diagnosis of primary breast malignancy, for whom surgery is planned to involve either partial or total mastectomy based on mammography, ultrasound and core biopsy or cytological examinations. The participants will be randomized either to additional imaging with CEM or to no further preoperative imaging. The findings of CEM will be considered at a second MDT conference, at which changes may be made to the primary treatment plan. The inclusion and exclusion criteria are given in Table 1.

**Table 1 Tab1:** Inclusion and exclusion criteria

**Inclusion criteria**	Planned primary surgery for suspected or verified primary breast malignancy
	Age ≥ 18 years
	Signed informed consent
**Exclusion criteria**	Planned neoadjuvant therapy
	On-going pregnancy
	Iodinated contrast agent allergy
	Renal disease or abnormal S-creatinin (normal range 45–90 μmol/l)
	Untreated thyrotoxicosis (including multinodular goitre) (upon suspicion check P-thyrotropin level, exclusion if < 0.4 mIE/l)
	Severe heart failure
	Myastenia gravis
	Breast implant
	Local recurrence as index lesion
	Inability to understand oral or written information about the study

Study inclusion started in November 2020 and inclusion of the required number of participants is expected to take between two and 3 years depending on the ongoing pandemic of Covid-19. Patients diagnosed at the breast centers in Helsingborg, Kristianstad and Halmstad in Sweden, will be included.

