### Pre- and postoperative assessment and data collection

At study inclusion, a primary treatment plan must have been decided upon, based on information obtained from findings at mammography, ultrasound, and core biopsy/cytology, according to current clinical standards. (Additional file 3). This plan may be subject to change after the clinical examination at the appointment when the diagnosis is given to the patient, as a result of findings of a larger or smaller tumor size in relation to breast volume, or due to comorbidity that may contraindicate a certain treatment. Any changes in the primary treatment plan after clinical examination must be clearly documented and motivated before CEM. (Additional file 5).

At the CEM examination, suspicious malignant findings will be noted according to a predefined protocol and if malignant-suspicious areas not previously located are identified by CEM they will be subjected to US-guided biopsy. The results of CEM will then be discussed at a second MDT conference, and taken into consideration in the primary treatment plan. (Additional file 8).

The whole study population will answer a short study-specific questionnaire including questions regarding possible allergy to iodinated contrast agent, weight and height, pre- or post menopausality, use of oral contraceptives, hormone replacement therapy or endocrine treatment after breast cancer, on-going pregnancy or breast-feeding, other diseases, previous surgery or radiotherapy to the breasts, and breast implants. This questionnaire will be administered at the appointment when the patient is informed about the study. Patients will also answer the preoperative version of the Breast-Q™ questionnaires [23]. These are globally used and validated patient-reported outcome measures. The Breast-Q™ questionnaires are currently the only validated, disease-specific questionnaires designed to evaluate different aspects of health-related quality of life and patient satisfaction related to breast cancer surgery.

The renal function of patients will be checked (normal range of serum creatinine 45–90 μmol/l) before the study inclusion, as the iodinated contrast agent may affect renal function.

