### Statistical methods

#### Power calculation

Based on the assumption that treatment planning will be modified in 18% of patients undergoing CEM, 195 patients will be needed in each arm to show that this proportion is significantly larger than a null proportion of 10%, using a power of 90% and an alpha value (two-sided) of 5%. We will recruit 220 patients per arm (440 patients in total) to account for a drop-out rate of approximately 10%.

The power calculation for the number of participants in this study is based partly on the result of the feasibility study, in which changes were made in the treatment plan in 10 out of 47 cases (21%) after CEM [21]. In previous studies, CEM and MRI have shown similar sensitivity and specificity in breast imaging. The results of the present study will thus also be compared with those of the POMB study in which preoperative MRI was used [13] resulting in changes in the treatment plan in 18% of cases.

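### The primary question is tested as a single-arm proportion against an unsourced 10%; the control arm, which could measure plan changes that CEM did not cause, is not used for it

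*Protocol article*

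**What the plan says.** All references are to the protocol article.

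- **Test criterion (Power calculation).** The design assumes that "treatment planning will be modified in 18% of patients undergoing CEM". The stated goal, with 90% power at a two-sided 5% level, is evidence that "this proportion is significantly larger than a null proportion of 10"%. The size given is: "195 patients will be needed in each arm". No section gives a source or rationale for the 10%.
- **Role of the control arm (Study design).** A cohort study could have answered the primary endpoint; the control group is there because most secondary endpoints need one.
- **Where changes arise (Patient enrollment).** "The findings of CEM will be considered at a second MDT conference, at which changes may be made to the primary treatment plan". The section on pre- and postoperative assessment likewise mentions the second conference only for CEM results.
- **Safeguards.** The Primary endpoint section confines the endpoint to changes that CEM findings lead to, in four categories: type of breast surgery, bilateral surgery, neoadjuvant therapy and axillary surgery. The section on pre- and postoperative assessment accepts that plans can change after clinical examination or for comorbidity, and requires: "Any changes in the primary treatment plan after clinical examination must be clearly documented and motivated before CEM".
- **External comparison (Power calculation).** "The results of the present study will thus also be compared with those of the POMB study in which preoperative MRI was used". The Background says that in that setting MRI was found to "lead to changes in the treatment plan in 18% of cases in a group of women younger than 56 years". Table 1 admits any adult.

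**The concern.** Added value is a comparative claim: what happens with CEM against what would have happened without it. A single-arm proportion answers it only if every counted change is caused by CEM, or if the null value is a credible rate of change without CEM. The article supports neither condition fully. A second multidisciplinary discussion may itself alter a plan, and whether a change counts as CEM-driven is a judgement made in a trial that the Randomization section describes as unblinded. The control arm could show how often treatment departs from plan without CEM, but the primary analysis puts an unsupported constant in its place.

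At stake is the meaning of the main result. A significant test would show that the counted proportion exceeds 10%, not how much of it is due to CEM. The comparison with the MRI trial adds a second weakness: that group was younger than 56, this trial has no upper age limit, and the Background itself says mammography is less sensitive in younger patients and in dense breasts.

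**Working it through.** **1. Reproducing 195.** Inputs from Power calculation: p0 = 0.10, p1 = 0.18, two-sided 5% (z = 1.960), 90% power (z = 1.2816).

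One-sample test against a fixed null:

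n0 = [(1.960·√(0.10·0.90) + 1.2816·√(0.18·0.82)) / 0.08]² = [(0.588 + 0.492) / 0.08]² = 182.4

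With continuity correction:

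n = (n0/4)·[1 + √(1 + 2/(n0·0.08))]² = 45.59 × 4.270 = 194.7, so 195.

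This matches the stated figure. Drop-out: 195/0.90 = 217, consistent with recruiting 220.

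A two-arm test of 18% against 10% does not give 195:

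n = [(1.960·√(2·0.14·0.86) + 1.2816·√(0.18·0.82 + 0.10·0.90)) / 0.08]², so 394 per arm.

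The sizing is therefore one-sample, which agrees with the Study design section.

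**2. What the primary test can and cannot exclude.** With n = 195, the exact binomial test rejects 10% at 29 or more changes (29/195 = 14.9%); its power at 18% is 89.3%. Suppose CEM contributed nothing, but a fraction b of the arm had a change that was counted as CEM-driven. The documents give no value for b, so these are assumptions:

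| b | Probability of a significant result |
|---|---|
| 8% or less | under 0.1% |
| 10% | 2.0% |
| 12% | 13.2% |
| 15% | 55.1% |

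A false positive is a problem only if b exceeds 10%. If b is lower, the test is safe, but the observed proportion may still overstate what CEM contributes, by an amount that is not measured.

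**3. What a supporting between-arm comparison would deliver.** Assumptions: 195 evaluable per arm and a total rate of 18% in Arm A. The control rate pc is not in the documents. With pooled variance under the null and p̄ = (0.18 + pc)/2:

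Power = Φ{[(0.18 − pc)·√195 − 1.960·√(2p̄(1−p̄))] / √(0.1476 + pc(1−pc))}

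Half-width of the 95% CI = 1.960·√[(0.1476 + pc(1−pc))/195]

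| pc | Power | Half-width (points) |
|---|---|---|
| 5% | 98.2% | 6.2 |
| 7% | 91.0% | 6.5 |
| 8% | 83.8% | 6.6 |
| 10% | 62.5% | 6.8 |

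Example for pc = 10%: (0.08 × 13.964 − 0.962)/0.4874 = 0.319, and Φ(0.319) = 62.5%. Power of 90% holds up to a control rate of about 7%.

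**4. Comparison with the MRI trial, restricted by age.** The age mix is not given. If 20% to 40% of Arm A are younger than 56 (assumption), that is 39 to 78 of 195. Wilson 95% intervals near 18% are then 9.0% to 32.7% (7/39) and 11.0% to 27.9% (14/78).

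**The case against.** The strongest reply is that the design is disclosed and consistent. Study design says openly that the control arm serves the secondary endpoints, and the sample size matches that choice. The endpoint counts only changes that CEM findings lead to, and the non-CEM causes the article names (clinical examination, comorbidity) are to be recorded before CEM. How attribution is recorded at the second conference may be set out in the additional files, which are not shown. Randomised comparisons do exist for reoperation and avoidable mastectomies, and the health-economic evaluation lists treatment changes among its benefit categories. Most of this stands, and it rules out several stronger readings:

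- *A reader might infer that non-CEM changes will be credited to CEM.* The documents support only that they can be: the safeguards remove the named sources and leave re-discussion and judgement.
- *A reader might infer that a near-automatic between-arm test decides the trial, because Arm B has no second conference.* Six changes among 195 against none would give a two-sided Fisher p of 0.030. But Statistical analyses offers Fisher's test only where applicable and does not assign it to the primary endpoint; the stated criterion needs at least 29 changes in 195.
- *A reader might infer from the phrase on each arm that a two-arm test is planned and underpowered, since it would need 394 per arm.* The reproduction of 195 and the Study design section show otherwise.
- *A reader might infer that the MRI trial is the yardstick for success.* It is an additional comparison and the origin of an 18% figure; the test criterion is the 10%.

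What does not answer the point is that the choice was disclosed. Disclosure does not measure the remaining non-CEM changes, and the arm that could measure them is already in the trial.

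**Conclusion.** The point holds as a limitation of the design that can be reduced cheaply, not as an error that invalidates the primary test. The primary result is a single-arm proportion against an unsourced 10%, and it cannot show how much of the observed change is attributable to CEM. The size of the possible overstatement is unknown, because the documents give no rate of change without CEM. If that rate, as counted, is 8% or less, a false-positive primary result is very unlikely (under 0.1%); it becomes material only above 10% (13.2% at 12%, 55.1% at 15%). The between-arm comparison is informative at the planned size if the control rate is about 7% or lower and weak near 10%. These statements rest on 195 evaluable patients per arm, 18% in Arm A, and assumed background rates. Separately, comparing an all-adult trial with an MRI group younger than 56 is open to confounding by age.

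**What to change.** Keep the primary test as planned and make two additions.

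1. **Supporting analysis in both arms.** Compare the treatment plan as documented after clinical examination (before CEM in Arm A, at the same point in Arm B) with the first treatment actually given, using the four categories of the primary endpoint. Report the Arm A minus Arm B risk difference with a 95% CI, stratified by site. Rest any causal statement that CEM changes treatment on this difference. State its precision and power in advance, including that power is about 63% if the control rate is 10%. Starting from the plan after examination preserves the separation that the protocol already makes.
2. **MRI comparison.** Restrict it to Arm A women younger than 56 and label it descriptive.

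The cost is one derived variable and one table, taken from medical records that are already a data source; no extra patients or procedures are needed. The downsides are that the attributable figure may be lower than the raw Arm A proportion, power is limited if background change is near 10%, and the interval in the under-56 subgroup will be wide.
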